### Informed consent

All subjects must sign informed consent to participate in the study. This consent form fulfills the requirements set forth by the Institutional Review Board (IRB) of MD Anderson. Before signing the consent form, all relevant details and the voluntary nature of the research study, including its purpose, procedures, anticipated risks and benefits are discussed with the potential participant. This dietary study is considered low risk and Data Monitoring Committee exempt. The trial is monitored by the PI and study physicians.

### Study intervention

#### Pre-visit, equilibration and run-in

To establish the basal diet and microbiome and to track compliance with study procedures prior to randomization, eligible and enrolled participants are asked to provide a stool sample and to complete anthropometric, dietary and other assessments during the pre-visit (Fig. 3). In the event that a recent clinical evaluation is not on file for an interested participant, a finger prick glucose test may also be administered. In the subsequent run-in period, participants are asked to follow the control diet (usual diet excluding dry beans) for the first 4 weeks.

#### Randomization and follow-up visits (V0-V4)

Participants who complete the run-in are randomized to begin the intervention diet or to continue the control diet for an additional 8 weeks (Fig. 2). The randomization list was generated by an independent analyst and allocated by a research team member not directly interacting with participants. Participants are block-randomized according to no use vs. regular use of chronic disease medications (namely statins and metformin) commonly prescribed to our target population of overweight/obese high risk CR patients. The randomization visit (V0) and all subsequent trial visits require a fasting blood draw and are conducted in the morning. There are a total of 5 in-person visits every 4 weeks from the randomization visit. At each visit, anthropometry and blood pressure are measured. Medications and changes in health status are reviewed. In addition, a stool sample is brought to each visit (Fig. 3).

#### Ramp-up and dose

Participants are provided with a supply of pre-cooked, canned organic navy beans (*Phaseolus vulgaris*) [19–21] stored in water with sea salt. To examine dose-response and temporal effects and to avoid gastrointestinal (GI) discomfort, participants are counseled to incorporate the canned beans in to their usual diet in a stepwise fashion during the intervention sequence (Fig. 3). Participants begin by consuming ½ cup (1 serving) of beans over the 2 week ramp-up period. At the end of the ramp-up period, participants provide a stool sample by mail. Following the ramp-up, participants consume 1 cup (2 servings) per day for an additional 6 weeks. At week 8, participants who complete the intervention diet crossover to the control diet and vice versa. Two ½ cup servings (260 g) of canned navy beans provide 220 kcal, 14 g protein, 38 g carbohydrate (~ 12% of 2000 kcal diet), 16 g of fiber (~ 64%), 200 mg of sodium (~ 8%), 660 mg of potassium (~ 22%), 12% of daily value for calcium and 20% of daily value for iron.

#### Compliance, adherence, and adverse effects

In addition to in-person visits, the study coordinator and registered dietitian (RD) maintain regular contact with participants via email and phone, while assuring and tracking all study procedures. When on the intervention diet, participants are provided simple, tailored tips and recipes for incorporating the beans in to their usual diet pattern. Participants are asked to keep a “bean log” to record adherence and track GI discomfort. In addition to frequent web-based dietary assessments, the bean log includes a week-by-week daily record of the date, time, amount and meal or manner in which the beans were consumed. Participants are considered adherent if they consume ≥80% of the beans over the intervention period and follow the prescribed regimen on at least 5 days/week. If despite consultation with the RD, some participants still experience difficulties adding the beans to their diet on their own or have specific needs (e.g., air travel), bean crackers prepared by the MD Anderson Cancer Center Bionutrition Research Core kitchen are provided. Participants may also continue the dietary intervention at a reduced/tolerable dose. Of the 30 previous dry bean and CVD trials reviewed, 11 trials reported GI symptoms, such as upset stomach, flatulence, bloating, and increased stool frequency. Across previous similar studies ≤2 participants per trial dropped out due to symptoms [22, 23]. In our study, all adverse events are documented at the time of report, recorded, and reviewed with the study physician. Grade 3 or above adverse effects, according to the Common Terminology Criteria for Adverse Events (CTCAE) Version 5.0, are reviewed immediately with the study physician. If any of the Grade 3 or above adverse effects are deemed serious according to MD Anderson IRB policies, then the IRB is also notified immediately.

#### Withdrawal

Participants may withdraw from the study at any time during the run-in or over the course of the study period (Fig. 2). Reasons for withdrawal are recorded (e.g., intolerance or inability to consume the beans, or a reason unrelated to the intervention). We request that participants, if willing, return a final stool sample by mail.

#### Post-trial follow-up

To explore the post-trial feasibility and impact of diet change, we conduct extended follow-up of all participants who complete the trial to begin to assess whether a long-term increase in bean intake is feasible, maintainable, and/or desirable in our target population. We use both active and passive follow-up methods via email/telephone, and electronic patient records. We assess current dietary habits via the NCI-DHQ (at 6 months and 1-year post-trial completion), as well as health outcomes and results of any subsequent screening exams. Participants may request to cease contact at any time.

### Biospecimen and data collection

#### Stool and fasting blood sample collection

An in-home, fresh-frozen stool sample collection kit, similar to that used in the Human Microbiome Project (HMP) [24] and refined in our previous studies is provided to participants with detailed instructions during the clinic visit. The participant is instructed to collect a stool sample before each scheduled in-clinic visit or return it via pre-paid express mail. Upon receipt, samples are transferred to − 80 °C storage. Fasting blood is collected at each morning in-clinic visit and immediately processed.

#### Diet and lifestyle assessment

Standard computer/web-enabled risk factor questionnaires (REDCap) are used to establish baseline status and monitor deviations over the study period (Fig. 3: Pre, V0, V1, V2, V3, V4). Participant’s diet is continually assessed and monitored throughout the study via biweekly NCI-Automated Self-Administered 24HR (ASA-24) [25] in conjunction with a “past month” web-based NCI diet history questionnaire (DHQ; every 4 weeks) [26]. Physical activity levels are assessed and monitored via validated long- and short versions of the International Physical Activity Questionnaire (IPAQ) [27, 28].

#### Data quality and integrity

All data is stored in a password protected REDCap and MS Access database on a secure and routinely backed-up institutional server. Audits of selected subsets of data are performed to ensure that appropriate safeguards of participant privacy are maintained. Privacy safeguards include appropriate password protection and physical security for all computer systems. Additional quality assurance procedures include a data collection protocol documented in a protocol manual; and a two-stage editing procedure for survey data collection. This two-stage process consists of the initial review of the data collection form by a project member immediately following data collection followed by a second review by a project member who will record any significant deviations from the protocol. Data entry systems, whether via REDCap, scannable forms, or hand entry with verification, specifically provide field checks, range checks for continuous variables and valid value checks for categorical variables; checks for legitimate dates and times and logical consistency. A specific audit trail system that identifies the date, time, and individual making changes on the database is part of the data-entry system. During data collection, we issue reports weekly, or even following any new data entry, depending on the needs of the project or upon the request of the PI.

### Laboratory methods

#### Gut microbiome and metabolome

To examine the impact of a change in dry bean intake within the usual diet on the diversity and composition of the gut microbiome, we will conduct *16S* rRNA gene sequencing on all stool samples collected. Following evaluation of relationships with established blood and stool markers, we will select an informative subset of pre and post-intervention stool samples from participants with marked differences in response to the intervention (e.g., responders vs. non-responders) to conduct whole genome shot-gun (WGS) sequencing and mass spectrometry-based metabolomic profiling of the gut microbiome. This will be complemented by characterization of host pathways via blood-based metabolomics.

#### Microbiome sequencing and data processing

We utilize state-of-the-art methods developed and benchmarked by our collaborating laboratory [29–31]. Briefly, bacterial genomic DNA is extracted and amplified with Illumina barcoded primers and analyzed on the Illumina MiSeq (*16S*) and HiSeq (WGS) platforms. Bacterial mock community samples (QC standards) are routinely included in each run. Alpha and beta (within and between sample) diversity analyses are performed to assess community diversity and richness by calculating the number of observed species for each sample at various sequencing depths. ANOVA and supervised machine learning techniques are used to identify taxa at the level of phylum, class, genus and species that differ significantly in abundance and discriminate between defined parameters. Various clustering algorithms assess whether distinct microbiome clusters or community types are formed.

#### Fecal and serum marker analysis

Fecal surrogates of subclinical intestinal inflammation and gut integrity linked to obesity and CRC risk [32, 33] are measured via established ELISA methods [34]. Fasting serum adipokines and cytokines linked to obesity-driven cancer risk and survival [35–41] and the gut microbiome [42, 43] are assessed via multiplex assays. For comparison with previous dry bean trials a lipid panel (TG, total, HDL, LDL, and VLDL cholesterol) is processed on the day of blood sample collection in a standard manner by a CLIA-certified laboratory.

### Statistical considerations

#### Power

Based on parameters from bean trials of obese individuals that observed comparable changes in LDL cholesterol and inflammatory marker levels [44, 45], with an n of 60 we have > 80% power to detect ≥10% change in LDL levels at a 2-sided α = 0.001 (to account for multiple comparisons). Based on the observed diversity (Shannon Index) and standard deviation (mean 2.5, SD 0.6) among obese polyp patients from our pilot observational study [46, 47], we have > 80% power to detect ≥20% change in microbiome diversity at a 2-sided significance level of alpha = 0.001. For the correlation analyses of changes in the gut microbiome and changes in markers, we have > 80% power at α = 0.001 to detect a significant linear correlation coefficient “r” when the true value is 0.37 [48].

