## Methods/design

### Overview of trial design

The study is a prospective, randomized, crossover trial (Figs. 2 and 3) of increased dry bean intake added to the participant’s usual diet (Intervention Diet), as compared to the participant’s usual diet excluding dry beans (Control Diet). Following an equilibration (control diet) period, sixty eligible subjects are randomized to one of two diet sequences - Control Diet then Intervention Diet *or* Intervention Diet then Control diet - with each subject acting as their own control. Canned beans are provided during the intervention period and multiple measurements are obtained at baseline and follow-up during each diet period in the sequence. Participants are free-living during the study period and able to choose and prepare their own meals, but are asked to not change any of their other usual habits for the duration of the study. To assess and monitor habitual behavior and adherence, participants are asked to complete web-based assessments at various time points during the study.

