#### Data analysis

Change scores of outcomes will be based on the differences between the beginning and the end of each study period (Figs. 2 and 3); and by subtracting the change experienced over the control period from the change experienced over the intervention period. Paired t-tests will be conducted to assess whether there are significant differences between changes in each subject’s baseline and follow-up outcomes over the equilibration, control, and intervention period. Two-way ANOVA will be used to test for differences in the change scores by categories of other variables. Generalized linear mixed models (GLMMS) will be used to explore potential order or carry-over effects, and to adjust for other potential confounders and assess potential effect modifiers measured at pre-study and study visits. Hierarchically clustered phylotypes will be constructed by the similarity of their dynamics [31] across study periods and subjects and in relation to other variables, such as usual diet pattern.

To examine the effect of a dry bean intervention on the diversity and composition of the gut microbiome, the primary outcome measure will be changes in stool *16S* rRNA gene profiles at baseline and follow-up for each cross-over period. We will quantify the microbial diversity within each subject at each time point; and calculate change scores and construct GLMMs (see above) with repeated measurements (PROC MIXED). We will also construct hierarchically clustered phylotypes by the similarity of their dynamics [31] across study periods and subjects and in relation to other variables, such as usual diet pattern.

To examine the relationship between changes in the gut microbiome and changes in fecal and serum markers, we will follow the procedures described above to quantify changes; and to assess the effects of other variables on these changes. We will assess Spearman correlations of changes in the gut microbiome with changes in fecal and serum markers and employ computational methods to identify taxa associated with differences in serum and fecal markers [49].

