To explore relevant functional changes in the gut microbiome we will use a tiered approach. In the first round of analysis of *16S* rDNA data to determine whether and where additional resources should be used for more comprehensive metabolomic and metagenomic profiling, we will use and compare established methods to infer metabolic functional profiles from 16S level data [50, 51]. To assess which compounds are related to which bacteria, we will use a combination of statistical methods and computational tools, including cluster and network analysis coupled with correlation-based non-parametric methods to explore the relationship between host markers and metabolomic pathways, microbial metabolites and gut bacterial species [52]. Principal component and coordinate analyses (PCA & PCoA) will be performed to examine intrinsic clusters within the metabolomic and microbiomic data between the control and intervention diets. In addition, heat maps will be generated using a hierarchical clustering algorithm to visualize the differences within the data set. Differences in gut microbiome composition will be further assessed using a nonparametric test, as described previously [53]. The correlation matrix between the microbial metabolites and gut bacterial species will be generated using Spearman and other correlation methods to explore the functional impact of dry beans on the gut microbiome. For analyses in which the multiplicity of tests is an issue, we will use the false discovery rate to report appropriately adjusted significance levels.

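### The >80% power for a 20% change in Shannon diversity holds for a single paired difference but is not assured for the difference of changes that the analysis section defines, which also overstates a reversible effect by half

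*Protocol article*

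**What the plan says.** The article's Power section gives the diversity inputs as "standard deviation (mean 2.5, SD 0.6) among obese polyp patients", taken from an observational pilot study, and concludes that "we have > 80% power to detect ≥20% change in microbiome diversity at a 2-sided significance level of alpha = 0.001". The sample size of 60 is named earlier in that section, with the LDL statement, and agrees with the trial overview: "sixty eligible subjects are randomized to one of two diet sequences". The section does not say which change the power refers to, and it gives neither a within-person correlation nor an SD of change.

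The Data analysis section forms change scores from the beginning to the end of each period and then compares periods "by subtracting the change experienced over the control period from the change experienced over the intervention period". It also plans paired t-tests of the changes and, for diversity, mixed models with repeated measurements.

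The section on randomization and follow-up visits sets five visits, four weeks apart, starting at randomization (V0 to V4, weeks 0 to 16). The section on ramp-up and dose places the crossover at week 8. No washout is described.

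**The concern.** An SD across persons does not by itself give the SD of a within-person contrast. That depends on how many measurements enter the contrast, with what weights, and how strongly they correlate. A difference of two changes is noisier than one paired difference. Here it is noisier still, because the visit that ends period 1 also starts period 2 and so enters with double weight.

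The shared visit also affects what is estimated. In participants who eat beans first, the control-period baseline is taken at the end of eight weeks on beans. A return to the starting level then counts as a control-period decline and is added to the bean effect.

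Two things are at stake: whether the power promised for a primary outcome applies to the comparison the plan defines, and whether the reported difference can be read as the size of the bean effect.

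**Working it through.** **Inputs from the article.** n = 60; two-sided α = 0.001; Shannon mean 2.5, SD 0.6; target 20%, so 0.20 × 2.5 = 0.5 units. **Assumptions.** SD 0.6 at every visit; the same correlation ρ between any two visits; 30 participants per sequence. Power is from the noncentral t with 59 degrees of freedom (critical value about 3.46).

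**1. The plan's own figure.** One paired difference has SD 0.6·√(2(1−ρ)). At ρ = 0 this is 0.849, the noncentrality is 0.5·√60/0.849 = 4.56, and power is 86%. At ρ = 0.5 the SD is 0.600 and power is 99.8%. The stated >80% is reproduced.

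**2. SD of the stated contrast.** The period boundaries are V0, V2 and V4.
- Intervention first: (V2 − V0) − (V4 − V2) = 2·V2 − V0 − V4.
- Control first: (V4 − V2) − (V2 − V0) = −(2·V2 − V0 − V4).

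The weights sum to zero and their squares sum to 4 + 1 + 1 = 6, so the SD is 0.6·√(6(1−ρ)): 1.470 at ρ = 0, 1.315 at 0.2 and 1.039 at 0.5.

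**3. Mean of the stated contrast.** Let τ be the bean effect and p the fraction of it still present eight weeks after beans stop.
- Intervention first: τ − (pτ − τ) = (2 − p)τ.
- Control first: τ − 0 = τ.
- Average: (1.5 − p/2)τ.

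With full reversal (p = 0) the average is 1.5τ, made up of 2τ and τ. With full persistence (p = 1) it is τ.

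**4. Power of the stated contrast, τ = 0.5.** With full reversal the mean is 0.75. Participant means of 1.0 and 0.5 in the two sequences add 0.25² = 0.0625 to the variance. At ρ = 0 the SD is √(2.16 + 0.0625) = 1.491 and the noncentrality is 0.75·√60/1.491 = 3.90. With a contrast mean of only 0.5, the noncentrality at ρ = 0 is 0.5·√60/1.470 = 2.63.

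| ρ | Stated contrast, full reversal (mean 0.75) | Stated contrast, mean 0.5 | End-of-period contrast, full reversal |
|---|---|---|---|
| 0 | 67% | 22% | 86% |
| 0.2 | 80% | 32% | 94% |
| 0.5 | 97% | 60% | 99.8% |

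With a mean of 0.5, 80% power needs an SD of at most 0.894, so ρ = 1 − (0.894/0.6)²/6 = 0.63.

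**5. End-of-period contrast.** This is V2 against V4 within person, signed as beans minus control, with SD 0.6·√(2(1−ρ)) as in step 1. Its mean across sequences is ((1 − p)τ + τ)/2 = (1 − p/2)τ, which equals τ under full reversal. A period term costs one degree of freedom; power at ρ = 0 stays above 85%.

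**The case against.** The strongest defence is that the power statement is not an arithmetic error. It names no contrast, and its inputs give more than 80% for a single paired difference at any ρ ≥ 0. The subtraction is also not the only planned diversity analysis: a mixed model on the same three visits, with visit effects and full reversal, has the power of the end-of-period contrast (86% at ρ = 0). Both points stand, and they limit the finding to a mismatch between the powered quantity and the stated contrast.

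A reader might infer that true power is 22 to 60% and that the claim fails unless ρ reaches 0.63. The documents do not support that as the headline. It takes the extra variance from the shared visit but not the extra signal, while the Background and Discussion both describe diet-induced microbiome changes as easily reversed. Nor does anything in the article place ρ between 0 and 0.5.

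A reader might also set the 0.001 level against the later sentence on the false discovery rate. That sentence covers only analyses where multiplicity is an issue, and 0.001 may be a strict planning level, so no contradiction is shown. Loss of completers is not demonstrated either: the article allows withdrawal but forecasts no rate. The LDL figure rests on parameters from trials that are not shown, so no error there can be established.

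**Conclusion.** The >80% figure is correct for one paired difference and not assured for the difference of changes. Under the article's own expectation of reversal, the stated contrast falls short only when ρ is below about 0.2, with 67% as the figure at ρ = 0. If the contrast's true mean is only 0.5, as with full persistence, it falls short below about 0.63.

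The second consequence does not depend on ρ. With full reversal, a true effect of 0.5 units appears on average as 0.75, that is, 30% of the mean of 2.5 instead of 20%, and the inflation arises entirely in the intervention-first sequence.

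These figures rest on an assumed equal correlation between visits, SD 0.6 throughout, equal sequences and all 60 participants analysed.

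**What to change.** For the diversity comparison, replace the difference of changes with the within-person end-of-period contrast (end of the intervention period against end of the control period, V2 against V4, with a period term), or with the equivalent treatment effect from the mixed model already planned. State that the power figure refers to it. With full reversal this estimates τ itself and keeps power above 80% at n = 60 for any ρ ≥ 0.

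State the reversal assumption alongside it. By step 5, an effect that persists after crossover shrinks this contrast, down to half of τ if nothing reverses, so the planned examination of carry-over should be reported with it.

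If the change-score contrast is kept, restate its power with the assumed within-person correlation and say that it averages 1.5 times a reversible effect.

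The cost is a change of wording and one recalculation. No participants, visits or samples are added.

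### The stated > 80% power for a correlation of 0.37 at α = 0.001 cannot be reproduced from the printed n of 60; with one pair of changes per subject it is about 36%

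*Protocol article*

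**What the plan says.** The Power section opens with the sample size and the LDL claim, "with an n of 60 we have > 80% power to detect ≥10% change in LDL levels", tested "at a 2-sided α = 0.001 (to account for multiple comparisons"). The last sentence of the section turns to the correlation analyses: "we have > 80% power at α = 0.001 to detect a significant linear correlation coefficient “r” when the true value is 0.37". That sentence repeats neither the sample size nor whether the test is one- or two-sided. The Overview of trial design agrees with the sample size: "sixty eligible subjects are randomized to one of two diet sequences".

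The Data analysis section names the method: "We will assess Spearman correlations of changes in the gut microbiome with changes in fecal and serum markers". It describes change scores in two ways: as a change over each study period, and as a single contrast per subject formed "by subtracting the change experienced over the control period from the change experienced over the intervention period". It does not say which of the two enters the correlations.

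**The concern.** A correlation of 0.37 is moderate, α = 0.001 is strict, and 60 pairs is a small sample for that combination, so a claim of more than 80% power calls for a check. The Hypotheses and objectives section expects microbiome changes to correlate with changes in metabolites and host biomarkers, and the Data analysis section gives this question its own paragraph. If the power figure is too high, a null result could be taken as evidence against correlations of 0.37 or more when the trial had little chance of detecting one of that size. There is also a mismatch of method, because power is given for a linear correlation while the planned analysis is Spearman.

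**Working it through.** **Inputs from the protocol article.** n = 60 (Power; Overview of trial design). α = 0.001 and true r = 0.37 (Power). Two-sided testing is stated for LDL and diversity but not restated for the correlation, so both versions were tried.

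**Input not in the document.** A variance factor of 1.06 for Spearman relative to the linear correlation. This is a standard approximation, used here as an assumption.

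**Formula (Fisher z).** Power = Φ(atanh(r) × √(n − 3) − z), where z is the critical value.

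**1. Attempt to reproduce > 80% from the printed inputs.** atanh(0.37) = 0.388 and √57 = 7.55, with product 2.93.
- Two-sided α = 0.001, z = 3.29: Φ(2.93 − 3.29) = 36.0%. Simulating the exact t-test of r (100,000 runs) gives 35.5%.
- With the Fisher bias term: 36.9%. Treating one variable as fixed (noncentral t): 36.4%.
- One-sided α = 0.001, z = 3.09: 43.7%.
- Spearman: 2.93/√1.06 = 2.85, so Φ(2.85 − 3.29) = 32.9%.

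No variant with 60 independent pairs at α = 0.001 comes near 80%.

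**2. What 60 pairs can detect.** For 80% power at two-sided α = 0.001:
- Linear: r = tanh((3.29 + 0.84)/√57) = 0.499, about 0.50.
- Spearman: tanh((3.29 + 0.84) × √1.06/√57) = 0.51.

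**3. Pairs needed for r = 0.37.** n = ((3.29 + 0.84)/0.388)² + 3 = 116.2, so 117 independent pairs.

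**4. Inputs that would give more than 80%.**

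| Pairs | α (two-sided) | Power at r = 0.37 | r with 80% power |
|---|---|---|---|
| 60 | 0.05 | 83.5% (simulated 84.0%) | 0.355 |
| 120 (60 subjects × 2 periods) | 0.001 | 81.9% (simulated 81.8%) | 0.364 |

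Both exceed 80%. The second keeps the printed α, and its detectable r of 0.364 becomes 0.37 when rounded up.

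**5. Does the 120-pair reading hold for the planned analysis?**
- Spearman with 120 fully independent pairs: 78.5%, below the claim.
- The two pairs from one subject may be dependent. As a rough illustration, assume a variance inflation of 1 plus the product of the between-period correlations of the two variables. A product of 0 leaves 82%. A product of 0.25 gives an effective n of 120/1.25 = 96 and power of about 68%. A product of 1 returns the calculation to 60 pairs and 36%.

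**6. Fewer completers.** The protocol gives no dropout rate, so these counts are assumptions. With one pair per subject at two-sided α = 0.001, 54 completers give 30% and 48 give 25%.

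**The case against.** The strongest reply concerns the unit of analysis. The figure of 36% assumes one pair per subject, whereas a crossover yields two period changes per subject and the Data analysis section does define a change for each period. The correlation sentence does not repeat n = 60, and it cites a source that is not at hand. With 120 pairs at the printed α, power is 82%. This is a fair point, and it means that 36% belongs to one reading of the unit of analysis. It does not rescue the sentence. The only n in the section is 60, the 120-pair count is an inference, the two pairs from a subject would have to be independent, and the planned Spearman test would still fall just short of 80%.

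A reader might go further and infer that 0.37 was calculated at α = 0.05 and then labelled 0.001. The arithmetic allows this, since 60 pairs at α = 0.05 give 83%, but the document does not support it as a diagnosis. The 120-pair reading fits 0.37 at least as well without changing the printed α, and nothing in the text favours one explanation over the other.

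It can also be said that the Data analysis section uses the false discovery rate where multiplicity matters, so 0.001 may not be the threshold finally applied. That may be so, but the power sentence makes its claim at 0.001 and has to be right at that level.

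**Conclusion.** The concern holds in this form: on its printed inputs the > 80% figure is wrong. With 60 subjects each contributing one pair of change scores, power at a true correlation of 0.37 and two-sided α = 0.001 is about 36%, so a correlation of that size would be missed about 64% of the time. The figure is 44% for a one-sided test and about 33% for Spearman. More than 80% requires either about 117 independent pairs or a looser α, and the document states neither.

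Which input slipped cannot be determined. The figures rest on the Fisher z approximation, confirmed by simulation for the linear correlation, and the Spearman values rest on the assumed factor of 1.06. The values for 54 and 48 completers are illustrations only. The error lies in the power statement; it does not touch the validity of the planned correlation analysis.

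**What to change.** Restate the sentence: with 60 pairs of change scores, one per subject, there is 80% power at two-sided α = 0.001 to detect a true correlation of about 0.50 (0.51 for Spearman).

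If both period changes per subject are to be correlated, state the number of pairs, say how within-subject dependence is taken into account, and recompute the detectable correlation for the Spearman test at α = 0.001.

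Do not keep 0.37 by moving to α = 0.05. The Power section adopts 0.001 to allow for multiple comparisons, and the correlation analyses involve many tests.

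The change is to wording only and leaves sample size, outcomes and conduct as they are. Its cost is a less favourable stated figure: a null result could not then be presented as a well-powered exclusion of correlations between 0.37 and about 0.50.
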